### Statistical analysis

All statistical tests will be conducted at a significance level of α = 0.05, with effect sizes measured using partial eta squared (η²p). The statistical power is set at 0.80, and all analyses will be performed using IBM SPSS Statistics 27.0. This study will adopt a 2 (Time: pre-test vs. post-test) × 3 (Group: mental fatigue–music intervention group, mental fatigue–non-music group, control group) mixed-design repeated measures ANOVA to examine the effects of mental fatigue and music intervention on golf-specific skill performance. The core hypothesis of the study is the time × group interaction effect, which aims to determine the performance differences across groups before and after the intervention, thereby verifying the potential value of music intervention under mental fatigue. Time main effects and group main effects will serve as secondary analysis objectives.

Prior to the main analysis, a one-way ANOVA will be conducted to compare baseline skill performance across the three groups to assess initial group equivalence and ensure the validity of subsequent comparisons. In the main effects analysis, mixed-design repeated measures ANOVA will be used to test the time main effect (whether overall skill performance changes over time), group main effect (whether there are overall differences among the three groups), and the time × group interaction effect (whether skill performance changes differ among the groups). If the assumption of sphericity is violated, the Greenhouse-Geisser or Huynh-Feldt correction will be applied to adjust the degrees of freedom. If the interaction effect is significant, simple effects analysis will be conducted to clarify the performance trends before and after the intervention within each group and to compare differences between groups at each time point.

To control the accumulation of Type I error due to multiple comparisons, all post hoc group comparisons will apply Bonferroni correction. If the study involves multiple primary outcomes or multiple independent hypothesis tests, the Holm-Bonferroni method will be further applied to control the family-wise error rate. In addition, the study will predefine a single primary outcome—ball-shooting accuracy score—while other technical indicators such as shot quality and reaction time will be treated as exploratory outcomes, serving to support and interpret the results but not as primary hypothesis testing targets.

All statistical analyses will report effect size indicators. For significant results, partial eta squared (η²p) will be reported as the effect size for ANOVA, and Cohen’s d will be calculated for between-group differences to reflect the practical significance of the effects. In addition to traditional significance testing, Bayesian factor analysis (Bayes Factor Analysis) will be conducted, and BF₁₀ values will be reported to provide relative evidence strength between the null and alternative hypotheses, enhancing the multidimensional reliability of the interpretations.

This study is designed as a closed golf summer training camp, and all experimental measurements will be conducted within a unified time window. This centrally managed experimental environment helps to minimize the risk of dropouts or missing data due to personal factors (such as going out, absences), but the risk of missing data in repeated measures design still needs to be considered. Missing data will be handled using mixed-effects models combined with maximum likelihood estimation (ML) to retain all available data and obtain robust and unbiased effect estimates. When the proportion of missing data is high (such as more than 5%), multiple imputation will be adopted, and sensitivity analyses will be conducted to explore the impact of the missing data mechanism on study conclusions, thereby enhancing the credibility of the inferences.

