### Participants

Following recommendations from Lakens [49] and Aberson [50], powering for interaction effects is considered essential in behavioral intervention trials where the primary interest lies in differential changes across conditions. Accordingly, the sample size calculation is based on the statistical power required to detect a time × group interaction effect, estimated using the “ANOVA: Repeated measures, within–between interaction” model in G*Power 3.1. Assuming a medium effect size f = 0.25 (Cohen’s standard), α = 0.05, power = 0.95, three groups, two measurement time points, and an intra-class correlation (ICC) of 0.5, the estimated result shows that the study requires at least 66 participants (22 per group) to ensure sufficient power for detecting the interaction effect. Considering a potential dropout rate of 15% [51], a total of 76 golfers will be recruited. If practical resource constraints result in a slightly smaller sample size, the study will report effect sizes and Bayes factors to supplement the interpretation of statistical significance and cautiously delimit the generalizability of conclusions to ensure the scientific rigor and interpretability of the results.

Participants in this study will be selected from the National Colleges and Universities Golf Championship (NCUGC) in China. The research team will collaborate with the head coaches of the participating teams to determine the universities willing to participate. Subsequently, the head coaches and team physicians will conduct an initial screening of players based on the inclusion criteria set for this study (Table 1). The research team will then verify the eligibility of the selected participants before the experiment begins.

**Table 1 pone.0337905.t001:** Participant selection criteria.

Inclusion criteria	Exclusion criteria
Aged 18–24 years old	Color blindness
Golfers of the NCUGC	Hearing loss
Least 3 years of specialized golf training	Insomnia
Least 5 trainings per week	Experiencing any physical injury
	Experiencing mental health issues
	Receiving any medication

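### The primary time × group test is valid but makes poor use of the baseline score; the baseline significance test and the open 5% switch to imputation should be removed

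*Protocol article*

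**What the plan says.** The Statistical analysis section specifies a 2 (time) × 3 (group) "mixed-design repeated measures ANOVA to examine the effects of mental fatigue and music intervention on golf-specific skill performance" and states that "The core hypothesis of the study is the time × group interaction effect". Before that analysis, "a one-way ANOVA will be conducted to compare baseline skill performance across the three groups to assess initial group equivalence"; the section adds that this is meant to secure the validity of the later comparisons, but gives no action if the test is significant. Missing data go first to a mixed-effects model fitted by maximum likelihood. Then, "When the proportion of missing data is high (such as more than 5%), multiple imputation will be adopted", with sensitivity analyses. The article names no baseline-adjusted model.

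The Participants section sizes the trial on the same interaction: "medium effect size f = 0.25", "α = 0.05, power = 0.95, three groups, two measurement time points" and a correlation of 0.5. This gives 66 golfers (22 per group), raised to 76 for 15% dropout. The Experimental design section puts baseline testing before the formal experiment, and random assignment within the formal experiment. The baseline score is therefore a pre-randomisation measurement.

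**The concern.** Three choices in one section bear on the same primary result.

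- **Model.** The interaction test subtracts the baseline in full, whatever its correlation with the post-test. Unless that correlation is very high, this adds noise that regression on baseline would remove. In a trial of 22 per group, precision already paid for is given away.
- **Baseline test.** Under proper randomisation any baseline difference is due to chance. A non-significant result does not show equivalence, and a significant one leads to no stated action. Yet chance imbalance is where a change-score test behaves worst, because of regression to the mean.
- **Missing data.** The 5% figure is offered only as an example, and the plan does not say whether missingness is counted per golfer or per score. Whether the primary p-value comes from a likelihood model or from imputation can therefore be settled after the data are seen.

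**Working it through.** **Inputs.** f = 0.25, ρ = 0.5, three groups, two time points and N = 66 (Participants); α = 0.05 (Participants and Statistical analysis). The Participants section uses power 0.95 and the Statistical analysis section says "The statistical power is set at 0.80". The 66 corresponds to 0.95, so that is the figure reproduced here.

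**Step 1: the plan's own figure.** For the within–between interaction, λ = f² × N × 2/(1 − ρ), with 2 and N − 3 degrees of freedom.
- λ = 0.0625 × 66 × 2/0.5 = 16.5 on 2 and 63 df, so power = 0.953.
- The smallest N for 0.95 is 65, or 66 in equal groups. The stated 66 is reproduced.

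**Step 2: variance ratio.** Take equal pre- and post-test variances σ². The change score has variance 2σ²(1 − ρ), and the baseline-adjusted residual has variance σ²(1 − ρ²). The ratio is (1 − ρ²)/[2(1 − ρ)] = (1 + ρ)/2, which is 0.75 at ρ = 0.5.

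Standard error of a difference between two groups of 22, in SD units at ρ = 0.5:
- change score: √(2 × 0.5 × 2/22) = 0.302
- post-test alone: √(2/22) = 0.302
- baseline-adjusted: √(0.75 × 2/22) = 0.261

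At the planned correlation the change score is no more precise than ignoring the baseline.

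**Step 3: power of the omnibus test under the same alternative.** Multiply λ by 2/(1 + ρ) and use N − 4 for the denominator df. At ρ = 0.5, λ = 16.5 × 2/1.5 = 22.0 on 2 and 62 df, so power = 0.989. The plan gives no data for ρ, so a range is shown, with f held at 0.25:

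| ρ | Variance ratio | Power at 66, interaction | Power at 66, adjusted | N for 0.95 (equal groups), interaction | N for 0.95 (equal groups), adjusted |
|---|---|---|---|---|---|
| 0.3 | 0.65 | 0.860 | 0.969 | 90 | 60 |
| 0.5 | 0.75 | 0.953 | 0.989 | 66 | 51 |
| 0.7 | 0.85 | 0.998 | 0.999 | 42 | 36 |
| 0.9 | 0.95 | >0.999 | >0.999 | 18 | 18 |

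Simulation at ρ = 0.5 (20,000 trials) gave 0.954 and 0.987.

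**Step 4: chance imbalance.** In 40,000 simulated null trials (22 per group, ρ = 0.5), overall type I error was 5.0% for both analyses. The baseline test was significant in 5.0% of trials, as it must be. Within those trials, type I error was 16.7% for the interaction test and 4.6% for the adjusted analysis.

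**Step 5: the 5% switch.** Counted per golfer, 5% of 76 is 3.8, so four losses trigger it. Counted per score, 5% of 152 is 7.6, so eight lost post-tests trigger it. Binomial probability of crossing the threshold, if losses follow randomisation:

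| Loss rate | Per golfer | Per score |
|---|---|---|
| 15% | 0.998 | 0.90 |
| 5% | 0.53 | 0.04 |

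**The case against.** The planned ANOVA is a recognised, valid analysis. It is prespecified, it matches the test used for the sample size, and its overall type I error is 5%. On the plan's own assumptions its power is already 0.953, so adjustment adds under four percentage points, and less at higher correlations. All of this stands: the model strand concerns precision and robustness, not error.

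A reader might infer larger gains from pairwise contrasts. At ρ = 0.5 and 22 per group, music versus no music under fatigue goes from 0.37 to 0.47 for a 0.5 SD difference. But that effect size is not in the document, the contrast is not the stated core test, and those figures ignore the planned Bonferroni correction.

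A reader might also infer that the named ANOVA would almost never be the analysis run, since 15% dropout is planned for. The article does not establish this. The 15% is a recruitment allowance. Baseline and formal testing are a week apart and assignment comes in the formal phase, so losses in that week may precede randomisation. The closed camp is expected to limit dropout, and the counting rule alone moves the probability widely. The likelihood mixed model is in any case essentially the same interaction test, so the only real switch is to imputation.

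Finally, no decision rule hangs on the baseline test, so it is too strong to say that the analysis relies on it. What remains is a validity role that such a test cannot fill.

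**Conclusion.** The point holds as one of efficiency and of fixing the method in advance, not of bias. At the plan's correlation a baseline-adjusted analysis has three quarters of the variance. Omnibus power at 66 goes from 0.953 to 0.989, and the larger benefit is protection if the correlation is lower (0.860 against 0.969 at 0.3). It also keeps its error rate near 5% when groups differ by chance at baseline, where the change-score test rises to about 17%. These figures assume equal pre- and post-test variances, a linear relation, baseline measured before randomisation and complete data.

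The baseline ANOVA cannot do the job it is given. The imputation threshold leaves the primary method open, but how often that would matter depends on post-randomisation losses and on how missingness is counted, neither of which the article settles.

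It would be tempting to say that a change of model cures all three. It does not: the baseline test and the switch have to be deleted in their own right.

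**What to change.** 1. Make the primary analysis one baseline-adjusted model of post-test accuracy by group, used whatever the level of missingness. A baseline-constrained mixed model by REML or ML is preferable, because it keeps golfers with a missing score. With complete data it has the same aim as ANCOVA. With missing scores the two are not equivalent, because plain ANCOVA drops those golfers.
2. Delete the baseline significance test and give descriptive baseline summaries by group.
3. Drop the 5% switch. Keep multiple imputation, or delta-adjusted imputation for departures from missing at random, as sensitivity analysis only.
4. Keep the 2 × 3 ANOVA as supportive if wanted. State in the Participants section that the 66 was derived for the interaction test and is conservative for the adjusted model (51 in equal groups would give 0.95 at ρ = 0.5).

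The cost is wording in two sections and one degree of freedom. Baseline is already collected, and the article says recruitment has not begun.

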Therefore, the aim of this study is to investigate the impact of music intervention on the golf-specific skill performance of Chinese golfers under mental fatigue. Through experimental research, the study will analyze whether music intervention can effectively mitigate the negative effects of mental fatigue and enhance the performance of golfers’ specialized skills. Additionally, the study will examine the differential impact of mental fatigue and music intervention on various skills. The findings will not only provide practical strategies for golf coaches and athletes to recover from mental fatigue and improve competitive performance under such conditions, but also offer valuable insights for other sports that require high concentration and resilience under pressure.

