### Experimental design

This study protocol is based on the SPIRIT 2013 clinical trial protocol guidelines [52,53] (S1-S3 File) and follows a randomized, controlled, partially-blind design. This study will be conducted during a specially designed summer golf training camp, with all experimental procedures carried out within the camp period. During this time, all participants will follow the same diet, daily schedule, training, and competition routines to minimize dropout and external interference. The study consists of three main phases (Fig 2): familiarization with the experimental procedure, baseline testing, and the formal experiment. During the formal experiment, participants will be randomly assigned to one of the following three groups: (MF-Mu Group) Participants undergo a mental fatigue induction task followed by a music intervention; (MF-nMu Group) Participants undergo a mental fatigue induction task but do not receive a music intervention; (CON Group) Participants neither undergo a mental fatigue induction task nor receive a music intervention.

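### The confirmatory test is a three-group interaction that the control group alone can make significant; the music comparison (MF-Mu versus MF-nMu) is neither designated nor powered

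*Protocol article*

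**What the plan says.** The Introduction sets the aim as finding out "whether music intervention can effectively mitigate the negative effects of mental fatigue" on golf skill.

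Experimental design defines three arms:
- MF-Mu: "Participants undergo a mental fatigue induction task followed by a music intervention".
- MF-nMu: "Participants undergo a mental fatigue induction task but do not receive a music intervention".
- CON: "Participants neither undergo a mental fatigue induction task nor receive a music intervention".

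The Statistical analysis section plans a 2 (time) × 3 (group) mixed ANOVA and states: "The core hypothesis of the study is the time × group interaction effect". It says that this test shows how performance differs across the groups before and after the intervention, "thereby verifying the potential value of music intervention under mental fatigue".

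Follow-up is conditional: "If the interaction effect is significant, simple effects analysis will be conducted to clarify the performance trends before and after the intervention". These simple effects are the pre/post trends inside every arm and comparisons of the arms at each time point. Post hoc group comparisons are Bonferroni-corrected.

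The Participants section bases the sample size on the same interaction: f = 0.25, α = 0.05, power 0.95, three groups, two time points and a correlation of 0.5, giving 66 golfers (22 per group).

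**The concern.** MF-Mu and MF-nMu both do the Stroop task and both then sit with earphones for 15 minutes; only the music differs. The question about music is therefore a question about this pair. The interaction test asks something wider, namely whether change differs anywhere among the three groups. The Intervention protocols section itself expects the Stroop task to reduce performance, so a gap between CON and the fatigued groups is anticipated whether or not music works.

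Two things are at stake. A significant interaction produced by fatigue alone would satisfy the core hypothesis and, on the plan's wording, count as support for music. And the 95% power describes the three-group test; the document gives no power for the music comparison.

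**Working it through.** **Inputs.** From Participants: f = 0.25, α = 0.05, correlation ρ = 0.5, two time points (m = 2), N = 66, n = 22 per group. The size of change in SD units is not given, so the patterns below are assumptions and a range is shown. A family of three pairwise comparisons is also assumed for the Bonferroni correction.

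**1. The plan's own figure.** λ = f²·N·m/(1 − ρ) = 0.0625 × 66 × 2/0.5 = 16.5, with 2 and 63 degrees of freedom. Power is 0.953. The stated 66 reproduces.

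**2. Translation to change scores.** With two time points, the interaction test equals a one-way ANOVA on change. The SD of change is σ√(2(1 − ρ)) = σ, so λ = n·Σ(δⱼ − δ̄)²/σ², where δⱼ is the mean change in group j.

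**3. No music effect.** Changes are 0 in CON and −d in both fatigued groups. Then Σ(δⱼ − δ̄)² = (2/3)d², in units of σ².

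| Fall d (SD) | λ = 22 × (2/3)d² | Probability that the interaction is significant |
|---|---|---|
| 0.5 | 3.67 | 0.37 |
| 0.8 | 9.39 | 0.77 |
| 1.06 | 16.5 | 0.95 |

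The last row solves 22 × (2/3)d² = 16.5, so d = √1.125 = 1.06. This is exactly the design effect, with nothing due to music.

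**4. Real music effect, scaled to the same f = 0.25.**
- Half of the loss reversed: CON 0, MF-Mu −d/2, MF-nMu −d. The sum of squares is d²/2, so d = √1.5 = 1.22 and the music difference is 0.61 SD.
- All of the loss reversed: CON 0, MF-Mu 0, MF-nMu −d. Here d, and the music difference, is 1.06 SD.

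The interaction has power 0.95 in both cases. For the music pair at post-test, the noncentrality is δ/√(2/22) for a difference δ in SD units, with 63 df and a two-sided level of 0.05/3 (critical t = 2.46). For a single baseline-adjusted contrast, the residual SD is √(1 − 0.5²) = 0.866, with 62 df and level 0.05 (critical t = 2.00).

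| Music difference | Noncentrality, post-test | Power, Bonferroni post-test | Noncentrality, adjusted | Power, single adjusted contrast |
|---|---|---|---|---|
| 0.61 SD | 2.03 | 0.34 | 2.35 | about 0.63 |
| 1.06 SD | 3.52 | 0.85 | 4.06 | 0.98 |

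For differences not tied to f = 0.25, the adjusted contrast has power of about 0.47 at 0.5 SD and 0.85 at 0.8 SD. The Bonferroni comparison has 0.22 and 0.58.

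**5. What the full planned sequence does when music has no effect.** Simulation with both fatigued groups falling 1.06 SD gives a significant interaction followed by a significant Bonferroni comparison of MF-Mu with MF-nMu in about 1.5% of trials.

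**The case against.** The strongest reply is that the music pair is not ignored. A significant interaction leads to corrected between-group comparisons, and Cohen's d and Bayes factors are reported as well. The stated purpose also covers mental fatigue, for which a three-group test is relevant. This stands in part. Followed to its last step, the sequence yields a false music difference in only about 1.5% of trials (step 5). What it does not cure is that the plan attaches the music conclusion to the interaction, names no pair as decisive and sizes the trial on the interaction alone.

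A reader might infer three stronger things, which the documents do not support:

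- *That making follow-up conditional on the interaction causes real music effects to be missed.* At the design effect size it costs almost nothing. In the half-reversal pattern, power is about 0.34 with or without that condition. The loss comes from the correction and from not adjusting for baseline.
- *That comparing groups at post-test is invalid.* The groups are randomised, so the comparison is unbiased. At a correlation of 0.5 it is as precise as a comparison of change. Baseline adjustment is a gain in efficiency.
- *That the within-group tests would often create a false picture of music protecting performance.* They run only after a significant interaction. With no music effect, MF-nMu significant and MF-Mu not significant then occurs in about 8% of trials for falls of 0.5 SD and in under 1% for falls of 1.06 SD. Such tests are still no evidence of a difference between groups.

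**Conclusion.** The point holds: the designated confirmatory test does not isolate music, and the comparison that does is neither designated nor powered. The exposure lies in reading the interaction as a music result and in low power for the music pair if the benefit is partial. The final pairwise comparison does not have an inflated error rate.

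The structural fault does not depend on any assumed effect size, but the percentages do. They rest on 22 completers per group, correlation 0.5, normal outcomes and three corrected pairs. If music reverses the whole loss at f = 0.25, even the planned comparison has power 0.85. The sample-size arithmetic for the interaction itself is correct.

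**What to change.** - Make MF-Mu minus MF-nMu in post-test accuracy, adjusted for baseline, the single primary contrast: two-sided α = 0.05, reported with a 95% confidence interval and not conditional on the interaction.
- Make MF-nMu minus CON the pre-specified secondary contrast for the fatigue effect.
- Keep the interaction F as supportive. Remove the statement that it verifies the value of music, and draw no music conclusion from it or from within-group pre/post tests.
- In Participants, restate power for the primary contrast over a range of differences. At 22 per group it is about 0.47, 0.63, 0.85 and 0.98 for 0.5, 0.61, 0.8 and 1.06 SD.

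The cost is wording and a stated power that may fall below 95%. The change requires no extra participants; the restated power shows openly which differences the planned size can detect. The article says that recruitment had not begun, so the contrast could still be fixed before any data were seen.

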### Intervention protocols

The experiment will be conducted at the university’s golf training facility under the supervision of professional members of the research team, including the university team’s head coach, team doctor, and a national-level golf referee. Data will be collected before and after the intervention, covering questionnaire assessments and golf skill tests. The baseline test and the formal test will be one week apart, and the experiment will take place on the same day of the week and at the same time (9:00–11:00 AM) to ensure sufficient recovery time and minimize the interference of residual effects [55,63,64].

During the mental fatigue induction phase, a 30-minute Stroop task will artificially induce mental fatigue, simulating the mental fatigue state that athletes experience during competitions or training sessions [65]. The Stroop task is a classic cognitive control task widely used for inducing mental fatigue. Research in sports science has shown that a 30-minute Stroop task significantly increases subjective fatigue and reduces sports performance [21,24]. This study will use a smartphone-based version of the Stroop task, where colour words (such as “red” and “blue”) are displayed continuously, but the font colour does not match the word’s meaning. Participants must ignore the word’s meaning and respond only based on the font colour. The Stroop task requires sustained attention, conflict resolution, and cognitive inhibition, leading to cognitive resource depletion and mental fatigue accumulation. During the experiment, all participants will use their smartphones (with brightness and touch sensitivity standardised) and wear earphones to minimise external distractions. Participants in the MF-Mu and MF-nMu groups will undergo mental fatigue induction, while those in the CON group will only read a golf magazine in a relaxed manner.

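### The time and group main effects, named as secondary objectives, do not cleanly estimate an intervention effect; baseline-adjusted post-test contrasts would

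*Protocol article*

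**What the plan says.** The model is fixed in the Statistical analysis section: "This study will adopt a 2 (Time: pre-test vs. post-test) × 3 (Group: mental fatigue–music intervention group, mental fatigue–non-music group, control group) mixed-design repeated measures ANOVA". The same section gives the priority of its effects: "The core hypothesis of the study is the time × group interaction effect", followed by "Time main effects and group main effects will serve as secondary analysis objectives". It defines the two secondary effects as "time main effect (whether overall skill performance changes over time") and "group main effect (whether there are overall differences among the three groups"). Simple effects, including group comparisons at each time point, follow only if the interaction is significant. Bonferroni correction applies to post hoc group comparisons.

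The timing comes from two other sections. Experimental design lists the phases as "familiarization with the experimental procedure, baseline testing, and the formal experiment" and adds: "During the formal experiment, participants will be randomly assigned to one of the following three groups". The baseline test therefore precedes randomisation. Intervention protocols states: "The baseline test and the formal test will be one week apart". Experimental design also places every procedure inside a camp in which all participants share one training and competition routine.

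**The concern.** A secondary objective should answer a question that the trial asks. The Introduction asks whether music offsets the harm that mental fatigue does to golf skills, and how both affect the separate skills. Neither main effect answers this.

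- **Group main effect.** It compares the average of pre-test and post-test between arms. No intervention can alter the pre-test, so half of what is averaged carries no effect.
- **Time main effect.** It averages the pre-post change over fatigued, fatigued-with-music and control participants, across a week of shared training plus a repeat of the same tests. A common gain would appear as a time effect with no intervention effect. A loss in one arm could be cancelled by a common gain.

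Both results would be reported as secondary findings. A non-significant group effect could be read as evidence against the interventions, and a significant time effect as evidence for them.

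**Working it through.** **Inputs.** From Participants: f = 0.25, α = 0.05, power 0.95, three groups (k = 3), two time points (m = 2), correlation ρ = 0.5, N = 66 (22 per group). Assumption: the ANOVA pre-test is the baseline test one week earlier. Test scores are scaled to SD 1.

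**1. The plan's own figure.** For the within-between interaction, λ = f²·N·m/(1−ρ) = 0.0625 × 66 × 2/0.5 = 16.5, with 2 and 63 df. Power is 0.953 at N = 66 and 0.944 at N = 63. The stated 66 reproduces.

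**2. The effect this implies.** The pre-post change has variance 2(1−ρ) = 1. With equal expected baselines, λ = N·s²/1 = 16.5 gives s = 0.5, where s is the SD of the three post-test group means.

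**3. Group main effect for the same post-test differences.** Each participant's average of the two tests has variance (1+ρ)/2 = 0.75, and the group means differ by half as much (0.25). So λ = 66 × 0.25²/0.75 = 5.5, with 2 and 63 df, and power is 0.524.

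**4. Omnibus post-test comparison adjusted for pre-test.** Residual variance is 1−ρ² = 0.75. So λ = 66 × 0.5²/0.75 = 22.0, with 2 and 62 df, and power is 0.989.

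**5. Other correlations, same post-test differences (s = 0.5).**

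| ρ | Group main effect: λ, power | Adjusted post-test, omnibus: λ, power |
|---|---|---|
| 0.3 | 6.35, 0.59 | 18.1, 0.97 |
| 0.5 | 5.5, 0.52 | 22.0, 0.99 |
| 0.7 | 4.85, 0.47 | 32.4, 0.999 |

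**6. Pairwise contrasts.** The pattern of means is an assumption. For equally spaced means −a, 0, a, 2a²/3 = 0.25, so a = 0.612. The adjusted contrast has SE = √(0.75 × 2/22) = 0.261.

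- Adjacent pair: 0.612/0.261 = 2.35, power about 0.64 at 0.05 and 0.52 at 0.025 (the first Holm step for two tests).
- The same pair as a contrast of group main-effect means: at ρ = 0.5 the SE is also 0.261, because (1+ρ)/2 = 1−ρ² = 0.75. The expected estimate is only 0.306, and 0.306/0.261 = 1.17 gives power of about 0.21 at 0.05.

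**7. Time main effect.** The documents give no size for a training gain, so these simulations (4,000 runs, 22 per group, ρ = 0.5) are illustrative.

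- Common gain of 0.3 SD, no intervention effect: time effect significant in 66% of runs, interaction in 5%.
- Loss of 0.6 SD in MF-nMu with a common gain of 0.2 SD: the expected mean change is (0.2 − 0.4 + 0.2)/3 = 0. The time effect was significant in 5% of runs, while the MF-Mu minus MF-nMu difference in change stayed at 0.60.

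**The case against.** The strongest defence is that the plan claims little for these effects. It rests its core hypothesis on the interaction, sizes the trial on the interaction alone, and defines the main effects accurately as overall change and overall differences. It does not call either one an intervention effect. All of that stands.

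The planned simple effects also include both post-test comparisons with CON. That stands in part: they run only after a significant interaction, and they are not adjusted for the pre-test.

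A reader might infer several stronger things that the documents do not support:

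- **That the trial's main conclusion is compromised.** It is not. The interaction removes any gain common to all arms.
- **That the group test has an inflated false-positive rate.** Over repeated randomisations it does not. A simulated lasting imbalance of 0.6 SD in one group, with no intervention effect, gave a significant group effect in 64% of runs. That figure is conditional on an assumed imbalance of about two standard errors (√(2/22) = 0.30).
- **That a null group effect is to be expected when the interventions work.** At ρ = 0.5 the chance is 1 − 0.52 = 48%, about even odds. It passes one half only at the higher correlation of 0.7 (53%).
- **That weather differs between the tests.** The documents do not mention weather, and they fix the same weekday and time of day.
- **That the replacement contrasts have power 0.99.** That figure belongs to the two-degree-of-freedom omnibus test. If music fully restores performance, MF-Mu versus CON has no difference to detect.

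**Conclusion.** The point holds as a weakness in the secondary objectives, not as an error in the primary analysis. The group main effect is a diluted estimate, half the post-test difference plus chance baseline imbalance. Its power is about 0.52 (0.47 to 0.59 for correlations 0.7 to 0.3) where the omnibus adjusted post-test test has 0.99 (0.97 to 0.999). The time main effect is an uncontrolled before-after change that can appear without an intervention effect or vanish despite one.

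The power figures rest on the plan's own inputs and on the pre-test being the baseline test. The pairwise figures also assume equally spaced means. The size of any training gain is unknown, so only the direction of that problem is established.

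**What to change.** In the Statistical analysis section:

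1. State that the time and group main effects are reported descriptively and carry no inferential objective.
2. Name two secondary objectives at post-test, each adjusted for the pre-test score: MF-nMu versus CON (did fatigue reduce performance) and MF-Mu versus CON (does a deficit remain after music). Give each a 95% CI, apply Holm adjustment across the two, and report both whether or not the interaction is significant.
3. If power is stated for these contrasts, give it per contrast with the assumed pattern of means, and do not quote the omnibus 0.99.

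The cost is analysis wording. The contrasts use scores the trial already plans to collect, and the article states that neither recruitment nor data collection had begun.
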